### 2.1. Trial Inclusion Criteria

A patient who, or whose legal representative, has provided written consent for the participation of the patient in the trial.A hospitalized patient with a confirmed diagnosis of COVID-19 based on a reverse transcription-PCR (RT-PCR) or loop-mediated isothermal amplification (LAMP) assay, antigen test, or other means.A patient who met all of the following criteria upon admission to a hospital:
○Patients who can begin receiving study treatment within 5 d after onset.○Patients with SpO_2_ ≥ 95% on room air.○Patients aged ≥ 40 years or having at least one of the following underlying diseases: renal impairment, chronic obstructive pulmonary disease, cardiovascular disease, cerebrovascular disorder, malignant tumor, obesity, diabetes mellitus, hypertension, and an immunosuppressive state.A patient aged at least 20 years at the time of informed consent.A patient who has been infected with SARS-CoV-2 for the first time.Our inclusion criteria have been chosen to ensure that the patients are appropriately and ethically included in our study, have a milder form of the disease, are in the appropriate age group, and do not already have SARS-CoV-2 antibodies at the point of enrollment.

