### 2.8. Observation and Test Parameters

Characteristics of each subject:
○Date of birth (age), sex, nationality/race, smoking history, complications, prior medical history, history of the current disease, and pregnancy status (premenopausal female subjects should undergo a pregnancy test).○Information on hospitalization (dates of admission and discharge).○Body height and weight.○Background data related to COVID-19 and overseas travel history.Physical findings:
○Status of supplemental oxygen and the use of mechanical ventilation.○Physical conditions will be examined by inspection, palpation, auscultation, and percussion.Vital signs:
○Level of consciousness○Body temperature (°C)○Blood pressure (mmHg)○Pulse rate (beats/min)○Respiratory rate (breaths/min)○SpO_2_ (%)Clinical condition:The clinical condition of each subject will be assessed according to the following:○Death○Hospitalization and the use of invasive mechanical ventilation or ECMO.○Hospitalization and the use of noninvasive mechanical ventilation or a high-flow oxygen device.○Hospitalization and supplemental oxygen requirement.○Not requiring hospitalization or supplemental oxygen but requiring the continuation of treatment (for COVID-19-related or other diseases).○Not requiring hospitalization, supplemental oxygen, or the continuation of treatment.○Not requiring hospitalization, but requiring the limitation of activities and/or oxygen therapy at home.○Not requiring hospitalization or the limitation of activities.Laboratory tests (Table 3)ImagingPlain chest X-ray

The appropriateness of the incorporated participants and the data collected were monitored on a regular basis to ensure quality.

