## Figures and Tables

**Table 1 life-12-00856-t001:** Secondary endpoints of the trial.

Objective	Endpoint	Rationale for the Endpoint
Prevention of mechanical ventilation or death.	Use of mechanical ventilation or death by days 14 and 28.	Prognosis is an endpoint that is not subjective.
Prevention of death.	Mortality on days 14 and 28.	Prognosis is an endpoint that is not subjective.
Prevention of the need for supplemental oxygen use.	Percentage of subjects who used oxygen on days 3, 5, 7, 14, and 28.	It is an endpoint that is not subjective.
To assess the shortening of the duration of symptoms (the time to clinical improvement).	Clinical improvement is defined as the first day a subject meets one of the three categories on the ordinal scale shown below: Not requiring hospitalization or supplemental oxygen and not requiring continuation of treatment. No hospitalization is needed but requires the limitation of activities and/or oxygen therapy at home. No hospitalization and no limitation of activities.	Clinical improvement is related to efficacy.
To assess clinical improvement on days 3, 5, 7, 14, and 28 in subjects given the convalescent plasma.	Clinical improvement on days 3, 5, 7, 14, and 28 (on an 8-point scale)	Clinical improvement is related to efficacy.
Time to improvement on the National Early Warning Score, UK (NEWS)	Time to discharge from the hospital or the maintenance of NEWS ≤2 for 24 h (whichever occurs first) NEWS on days 3, 5, 7, 14, and 28.	Clinical improvement is related to efficacy.
Decrease in the viral load in the convalescent plasma group after convalescent plasma transfusion.	Time-weighted average change and the numerical change in the SARS-CoV-2 virus load in nasopharyngeal swabs from day 0 to each day of assessment.	Change in the viral load has been used as the index of the therapeutic effect in many studies.
To assess safety after convalescent plasma transfusion.	Occurrence of adverse events.	It is necessary to evaluate safety.
To screen and identify variants.	Determine if variants are present in nasopharyngeal swab samples on day 0	Variants are related to efficacy because it has been reported that variants may reduce the antiviral activity of neutralizing antibodies.

**Table 2 life-12-00856-t002:** Study schedule.

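### The 8-point clinical scale has no level for an inpatient without oxygen, and its out-of-hospital levels overlap, which undermines two secondary endpoints

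*Protocol article*

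**What the plan says.** All references are to the protocol article. The levels carry no numbers there; they are numbered 1 to 8 here in the order of section 2.8.

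- **Entry state.** Section 2.1 enrols "A hospitalized patient with a confirmed diagnosis of COVID-19" and, among the criteria to be met on admission, "Patients with SpO_2_ ≥ 95% on room air".
- **Scale, levels 1 to 4.** Level 1 is death. Levels 2 to 4 are hospitalization with invasive ventilation or ECMO, with noninvasive ventilation or high-flow oxygen, and, as the mildest inpatient level, "Hospitalization and supplemental oxygen requirement".
- **Scale, levels 5 to 8.** Level 5: "Not requiring hospitalization or supplemental oxygen but requiring the continuation of treatment (for COVID-19-related or other diseases". Level 6: "Not requiring hospitalization, supplemental oxygen, or the continuation of treatment". Level 7: "Not requiring hospitalization, but requiring the limitation of activities and/or oxygen therapy at home". Level 8: "Not requiring hospitalization or the limitation of activities".
- **Endpoints.** Table 1 builds two secondary endpoints on the scale. One is "Clinical improvement on days 3, 5, 7, 14, and 28 (on an 8-point scale". The other is time to clinical improvement, defined as the first day in any of three categories, which correspond to levels 6, 7 and 8. Level 5 is not among them. Table 1 repeats the out-of-hospital wording for level 6.
- **Timing and rating.** Table 2 has the clinical condition rated before transfusion on day 0, daily in hospital, and on set days after discharge. Section 2.4 says that independent assessors could make blinding possible for clinical improvement, but leaves the trial unblinded.

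**The concern.** An ordinal scale used as an endpoint must give each subject exactly one level on each day. This one appears to fail in both directions. The trial's typical patient, in hospital and breathing room air, seems to have no level. A discharged subject seems to have two, because levels 5 and 6 ask about treatment and levels 7 and 8 ask a different question, with no rule saying which takes precedence.

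If so, sites must improvise a level for inpatients off oxygen, and after discharge the recorded level depends on which of two true statements the rater picks. Since raters know the allocation, part of any difference between arms on these endpoints could reflect rating practice rather than outcome.

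**Working it through.** The plan gives no figure to reproduce here. The check is whether the eight levels are exhaustive and mutually exclusive.

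**Inputs.** Four attributes that the level definitions use: in hospital or not; respiratory support (none, oxygen, noninvasive or high-flow, invasive or ECMO); treatment continuing or not; activity limited or not. Outside hospital only no oxygen or home oxygen is considered.

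**Number of living states.** In hospital: 4 × 2 × 2 = 16. Outside hospital: 2 × 2 × 2 = 8. Total: 24.

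**Matching each state to the wording of levels 2 to 8**, taking the hospitalization phrase as where the subject is:

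| State | Combinations | Levels that fit |
|---|---|---|
| In hospital, no oxygen | 4 | none |
| In hospital, with support | 12 | exactly one (2, 3 or 4) |
| Out, no oxygen, treatment, limited | 1 | 5 and 7 |
| Out, no oxygen, treatment, not limited | 1 | 5 and 8 |
| Out, no oxygen, no treatment, limited | 1 | 6 and 7 |
| Out, no oxygen, no treatment, not limited | 1 | 6 and 8 |
| Out, home oxygen, not limited (with or without treatment) | 2 | 7 and 8 |
| Out, home oxygen, limited (with or without treatment) | 2 | 7 |

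**Counts.** No level: 4. Exactly one level: 12 + 2 = 14. Two levels: 4 + 2 = 6. Check: 4 + 14 + 6 = 24. So 6 of the 8 out-of-hospital combinations are ambiguous. These are counts of combinations, not shares of patients.

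**Consequence for the fixed-day 8-point endpoint.** It has no valid level for any inpatient on room air on days 3, 5, 7, 14 or 28, and no unique level for most out-of-hospital states.

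**Consequence for time to clinical improvement.** Levels 7 and 8 together cover all 8 out-of-hospital combinations. Level 5 therefore lies wholly inside levels that count as improvement, although it is itself left out. If one level is recorded per day, a discharged subject off oxygen but still on treatment has the event or not according to whether level 5 or level 7/8 is chosen. If any matching level counts, the event becomes the first day out of hospital, and leaving out level 5 has no effect.

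**The case against.** **The missing level does not block both endpoints.** A reader might infer that neither can be scored. For time to clinical improvement, an inpatient on room air meets none of the three listed categories and simply has no event yet. This stands: only the overlap harms that endpoint.

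**Not every subject is in the missing state at the first rating.** The room-air criterion applies on admission, and Table 2 allows admission up to 3 days before day 0, so some subjects may be on oxygen by then. This stands: the statement is exact for admission only.

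**Entry-state subjects are not shown to be scored as improved on day 0.** A reader might infer this by placing a room-air inpatient in level 6. That requires taking the phrase about not requiring hospitalization as a medical judgement on someone still in a bed, whereas the finding that no level fits takes it as location. The two harms need different readings and cannot be added. The judgement reading does not rescue the scale either, since levels 5 to 8 would still overlap.

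**The size of any bias is unknown.** Simulated trials with identical true outcomes (100 per arm, 80% discharged, half of them on continuing treatment, no activity limitation, Wilcoxon test at two-sided 0.05, 4,000 runs) reject in about 5%, 14% and 39% of runs when level 8 is chosen over levels 5/6 in 50%, 60% and 70% of discharged subjects in one arm against 50% in the other. Every driver is assumed, and the article does not support any particular rating difference. The figures illustrate sensitivity and are not evidence of the size of a bias in this trial.

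**The full protocol is not shown.** Version 2.4 and Supplementary Information S4 may hold better wording, and site practice cannot be judged from the article. But the article prints the scale in full and repeats the level 6 wording in Table 1, so this is a stated rule that fails, not detail left to another document.

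**Conclusion.** The point holds in this form: as printed, the scale is neither exhaustive nor mutually exclusive. Of 24 living states, 4 fit no level (all inpatients without oxygen) and 6 fit two (6 of the 8 out-of-hospital combinations). The fixed-day 8-point endpoint lacks a valid level for the state in which subjects are admitted. Time to clinical improvement is ambiguous for discharged subjects off oxygen and still on treatment.

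This rests on the literal wording of section 2.8, with hospitalization read as location. How many subjects are affected, and whether ratings would differ by arm, cannot be determined from the article. The viral-load primary endpoint (section 2.5), the sample size (section 2.12) and the secondary endpoints that do not use this scale, such as mortality and oxygen use, are not affected.

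**What to change.** Reconcile section 2.8 and Table 1 so that each subject-day fits exactly one level. One workable form:

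- Levels 5 and 6: hospitalized without supplemental oxygen, with and without continuing treatment.
- Levels 7 and 8: not hospitalized, with and without activity limitation or home oxygen.

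Then change the matching category in Table 1 and restate which levels count as improvement.

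For data already collected, re-derive hospital status from admission and discharge dates, oxygen status from the physical findings, and treatment from the concomitant drug record. There are two limits. Activity limitation appears only inside the scale, so for a discharged subject rated 5 or 6 the split between levels 7 and 8 may not be recoverable. Physical findings, where oxygen status is listed, may be skipped after discharge from day 7 on (Table 2). Where the split cannot be recovered, merge levels 7 and 8 or report them as not distinguishable.

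The cost is a reworded list and table cell, a code-list change, some re-derivation, and possible loss of the 7/8 distinction. No new visits are needed. Section 2.10 scheduled observation to end on 31 March 2022, and the Background quotes figures as of 30 May 2022. If that schedule held, the code-list change comes too late for the ratings, and the correction has to be made in the derivation and reporting.

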### 2.9. Study Schedule

The study schedule is shown in Table 2. 

### 2.10. Participation and Follow-Up Periods

The subjects in both the convalescent plasma and standard of care groups will be followed up for up to 28 d to detect any adverse events. In addition, the convalescent plasma group will be examined for post-transfusion infections on day 90. The observation period for the trial will run from the day of registration of the first subject until 31 March 2022 (scheduled).

### 2.11. Potential Benefits and Risks of the Study Drug

See Supplementary Information S3.

### 2.12. Sample Size Calculation

The trial was designed to enroll 200 patients. We calculated that this sample size would provide 90% power to detect a between-group log viral load difference of 0.5 (SD 1.1) at the 0.05 (two-sided) level of significance, accounting for several drop-out subjects.

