### 2.15. Data Monitoring Committee

The committee was established to neutrally evaluate interim data during the study period and to provide appropriate advice and recommendations to ensure the safety of subjects and the ethical and scientific validity of the study. In fact, it was not conducted due to a lack of progress in incorporation.

In addition, the committee periodically evaluated the following:Changes over time in the treatment regimen in both treatment groupsRelationship between the quality of the study drug (Grades A to C) and safety

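### The 200 patients give about 90% power only if nobody is lost, so the stated allowance for drop-outs is not in the number

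*Protocol article*

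**What the plan says.** Section 2.12 (Sample Size Calculation) of the protocol article gives the whole justification in two sentences. The first is "The trial was designed to enroll 200 patients". The second begins "We calculated that this sample size would provide 90% power to detect a between-group log viral load difference of 0.5 (SD 1.1"), sets the test "at the 0.05 (two-sided) level of significance", and ends with "accounting for several drop-out subjects".

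Section 2.4 gives 1:1 randomisation. Section 2.5 makes the primary endpoint a time-weighted average change in nasopharyngeal viral load, a continuous outcome. Section 2.12 states no number or rate of drop-outs, no evaluable sample size and no test or formula.

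**The concern.** An enrolment figure that allows for drop-outs has to exceed the number of evaluable patients needed for the stated power. Here the printed inputs require slightly more evaluable patients than the trial enrols. The sentence makes two claims, that 200 gives 90% power and that this holds after some losses. Rounding can support the first, but it cannot support both.

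This sentence is the article's only statement of what the design can detect on the primary endpoint. A reader of a null result would take it that 90% power had survived attrition, when any attrition takes power further below that figure.

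**Working it through.** **Inputs.** Difference 0.5, SD 1.1, two-sided 0.05, power 90%, 200 enrolled (section 2.12); 1:1 allocation, so 100 per arm (section 2.4). The check is a two-sample comparison of means, by the normal approximation and by the noncentral t distribution.

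**Step 1: reproduce the stated power with no losses.**

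Power = Φ(δ / (σ√(2/n)) − 1.96), with n = 100 per arm:

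0.5 / (1.1 × √0.02) = 3.214; 3.214 − 1.960 = 1.254; Φ(1.254) = 0.895.

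The t version gives 0.892. Both are about 90%, so the stated power is reproduced when all 200 patients are evaluable.

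**Step 2: evaluable number needed for 90%.**

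n per arm = 2(1.96 + 1.2816)² × 1.1² / 0.5² = 101.7, so 102 per arm and 204 in total. The t test needs 103 per arm, 206 in total.

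The reserve for drop-outs is 200 − 204 = −4 (normal) or 200 − 206 = −6 (t). No allowance is left.

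**Step 3: power after losses.** The article gives no rate, so these losses are assumptions, split equally between arms.

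| Lost of 200 | Evaluable | Power, normal | Power, t |
|---|---|---|---|
| 0 | 200 | 89.5% | 89.2% |
| 4 (2%) | 196 | 88.9% | 88.6% |
| 10 (5%) | 190 | 88.0% | 87.6% |
| 20 (10%) | 180 | 86.2% | 85.8% |

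**Step 4: difference detectable with 90% power** (normal approximation), (1.96 + 1.2816) × 1.1 × √(2/n):

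- n = 100 per arm: 0.504
- n = 95 per arm: 0.517
- n = 90 per arm: 0.532

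**Step 5: can other readings of the inputs make room for losses?**

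- One-sided 0.05 needs 166 evaluable and would leave 34 spare, but the article states a two-sided test.
- 80% power needs 152 and 85% needs 174, but the article states 90%.
- To hold 90% power, the SD could be at most 1.091 with no losses, 1.063 with 10 lost and 1.035 with 20 lost. The last of these would be printed as 1.0, not 1.1.
- An unrounded SD of 1.05 (186 needed) or an unrounded difference of 0.52 (190 needed) would leave some room. The article states neither.

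**The case against.** The strongest reply is that the gap is trivial. With complete data the power is 89.5%, which anyone would report as 90%, and 204 or 206 against a round 200 is a difference of 2 to 3%. This stands. A reader might infer that 200 patients are too few for the stated power even with no losses, but the documents do not support calling that an error: it is ordinary rounding, and an SD of 1.09 before rounding gives exactly 200.

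Second, losses on this endpoint may be few. It uses swabs from day 0 to day 5 in patients who are in hospital at enrolment. Footnotes to Table 2 let discharged patients skip samples only from day 14, and ask for a swab when a patient discontinues up to day 14. If several means about four patients, power is still 88.9%, and the 10% case is only an illustration. This also stands, and it limits the size of the point.

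Third, the article condenses a fuller protocol, where unrounded inputs or covariate adjustment might have left a margin. That is possible, but section 2.12 prints its own inputs and its own conclusion, and on those inputs the drop-out allowance is absent. Nothing else in the article supplies it.

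A reader might also link this to section 2.15, where the data monitoring committee's evaluation is said not to have taken place: "In fact, it was not conducted due to a lack of progress in incorporation". That remark concerns the conduct of the trial. It gives no final number of patients and has no bearing on whether the planned calculation is right.

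**Conclusion.** Wrong as written, but minor. The 90% figure is acceptable for 200 evaluable patients; the claim that it already covers drop-outs is not supported by the printed inputs, because the evaluable need of 204 to 206 exceeds enrolment. At small early losses the shortfall from 90% is about 1 to 2 percentage points, and at 10% loss about 4 points.

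This rests on a two-sample comparison of means with the inputs taken at their printed values, equal losses in the two arms, no gain from covariate adjustment, and loss rates that are assumed because the article gives none. It does not show that the trial is materially underpowered as planned.

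**What to change.** Restate the last sentence of section 2.12 along these lines: *200 randomised patients give about 89-90% power with complete data to detect a difference of 0.5 (SD 1.1, two-sided 0.05), and about 88% or 86% if 5% or 10% have no primary endpoint.* An equivalent form keeps 90% power and attaches it to a difference of about 0.52 (5% missing) or 0.53 (10% missing). In either form, remove the statement that drop-outs are already accounted for.

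The cost is one sentence. Enrolment, endpoint and analysis do not change; the stated power becomes slightly less favourable.

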### 2.13. Statistical Analysis Plan

See Supplementary Information S4.

### 2.14. Safety Evaluation

See Supplementary Information S5.

### 2.15. Data Monitoring Committee

The committee was established to neutrally evaluate interim data during the study period and to provide appropriate advice and recommendations to ensure the safety of subjects and the ethical and scientific validity of the study. In fact, it was not conducted due to a lack of progress in incorporation.

In addition, the committee periodically evaluated the following:Changes over time in the treatment regimen in both treatment groupsRelationship between the quality of the study drug (Grades A to C) and safety

### 2.16. Data Management Team

The Director of the Joint Center for Researchers, Associates and Clinicians (JCRAC) Data Center designated a person to be in charge of data management tasks, and the data management staff carried out the tasks specified in the data management plan.

## 3. Discussion

COVID-19 is a significant public health concern because of its high associated morbidity and mortality. As of December 2020, the therapeutic agents approved for COVID-19 in Japan were limited to two drugs: remdesivir, an antiviral drug, granted a Special Approval for Emergency on 7 May 2020, and dexamethasone, which has an anti-inflammatory effect. Several case reports and clinical studies of convalescent plasma therapy have been reported [21,22,23,24,25,26,27,28,29], but the results have been conflicting. This could have occurred because the neutralizing antibody titer in the COVID-19 convalescent plasma administered was not measured in most studies, and there appears to be an association between a higher antibody index and severe COVID-19 [30]. Thus, in this trial, subjects will receive plasma with high neutralizing activity after it is determined whether the convalescent plasma from each donor can inhibit infection when susceptible living cells are exposed to infectious novel coronaviruses. The objective of this trial is to evaluate the efficacy of the convalescent plasma collected from donors who recovered from COVID-19.

There have been several important findings in nonclinical and clinical studies of relevance to this study. Purified IgG from convalescent plasma inhibited the cytotoxicity and replication competence of SARS-CoV-2 in an in vitro cell infection system. At a high concentration, it can completely inhibit SARS-CoV-2 infection at the single-cell level [18]. In a hamster model representing an in vivo cell infection system, the administration of convalescent plasma inhibited viral replication in the lung [31]. However, several RCTs of convalescent plasma therapy have already been conducted in countries outside Japan, but no conclusion has been reached with respect to the efficacy of convalescent plasma therapy, which is likely in part because of the heterogeneity of the types of target patients, interventions, and endpoints among trials [32]. Furthermore, it is well known that SARS-CoV-2 viruses have undergone multiple mutations since their appearance in 2019, resulting in changes in virulence that affect disease severity worldwide. Although it was reported that convalescent plasma therapy has led to a significant decrease in mortality rates among SARS-CoV-2 patients, the efficacy of the therapy would be affected by the degree of severity caused by multiple mutations of SARS-CoV-2 variants [25]. Further studies, such as on the early administration of convalescent plasma containing appropriate antibodies, will be needed to demonstrate the efficacy of convalescent plasma therapy. 

